**Table 1 T1:**
[figure not shown]
Study timeline according to the standard protocol items: recommendations for interventional trials (SPIRIT) diagram.

## Safety

3

We will conduct electrocardiogram, liver function, and renal function tests on all participants during the screening phase to exclude patients with severe organic damage. For recording the test period appeared adverse reactions, such as treatment in syncope, local irritation, infection, hemorrhage, stabbing pain unbearable, hysteresis, curved needle, needle acupuncture treatment for sustained severe local pain after 1 hours. Researchers should be on the watch list in cases recorded the degree of symptoms or disease, date of onset, frequency, duration, mitigation, treatment measures and treatment after date, results and follow-up. When an adverse event is found, the observing physician may decide whether to suspend the observation according to the condition. If serious adverse events occur, the unit undertaking the clinical trial shall immediately take necessary treatment measures to protect the safety of the subjects. All adverse events should be followed up and recorded in detail until they are properly resolved or stable.

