#### Lifestyle intervention

2.7.1

Patients in both groups will receive basic health management and lifestyle modification over the course of the 12-week study period. Lifestyle intervention is implemented with reference to the goal of primary prevention of type 2 diabetes in the Guidelines for the Prevention and Treatment of Type 2 Diabetes (2017 Version) in China.^[14]^

The first lecture on prediabetes will be held when the study begins, which is to include the development and prevention of diabetes. Prediabetes health education courses will be performed once a month. Course content includes:

(1)Diet: patients will be instructed to focus on low-sugar, low-salt, light and easily digestible foods, limit the total daily calories intake, reasonably control cholesterol and fat intake, and control body weight.(2)Living habits: patients will be instructed to work and rest on time. Bad habits such as smoking and drinking will be strictly controlled. Require patients to adhere to 50 minutes of moderate-intensity aerobic exercise at least 3 times per week.(3)Psychology: patient will be received psychological therapy to relieve patient's pressure, and to inform the patient that the cure or delay of prediabetes progress is likely. It should be treated with a positive and optimistic attitude, and do not be afraid or let it develop.

Researchers will personally understand the patient's lifestyle habits such as diet, rest time and exercise, and give reasonable personalized lifestyle suggestions. The researchers supervised the implementation of the prevention and treatment plan through telephone or Internet follow-up, encouraging family members to participate in intervention management methods to improve the self-management ability of prediabetes patients.

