**2.7.2.1.2.3 Treatment course**

The acupuncture session will be for 45 minutes. There will be 2 sessions per week for 12 weeks, giving 24 sessions in total.

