### Outcome measures

2.8

Data collection will be performed by a trained and nonparticipating evaluator who is blinded to the patient's assignment, including at baseline, the intervention phase (4 weeks, 8 weeks, and 12 weeks) and at the end of follow-up (24 weeks).

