## Statistical analysis

5

In this study, the conversion rate from IGT to normal blood glucose between baseline and follow-up period was the main outcome indicator. Statistical analysts will use a one-sided *t* test to compare between the 2 groups. The 2 groups will be compared using the 95% confidence interval method to determine the advantage. Data will be statistically analyzed using PASW Statistics 18.0 (IBM SPSS Inc., Armonk, NY) and SAS 9.2 software (SAS Institute Inc., Cary, NC). For secondary results, a 2-tailed *P* value *<* .5 will be considered statistically significant. For safety evaluation and analysis, first use descriptive analysis, and then use tests to compare the incidence of adverse reactions between the 2 groups. When comparing, consider the severity of adverse reactions and the degree of causation with the intervention. The categorical variables between the 2 groups were compared using Fisher exact test and chi-square test.

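### Adverse reactions possible in either arm could be recorded more often with acupuncture, because that arm alone has 24 extra clinician contacts before incidence is tested between arms

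*Protocol article*

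**What the plan says.** Safety is part of the trial's stated objective (Abstract and Introduction). Section 3 (Safety) records reactions that arise in the test period: "For recording the test period appeared adverse reactions, such as treatment in syncope, local irritation, infection, hemorrhage, stabbing pain unbearable, hysteresis, curved needle". It assigns the recording to the researchers and leaves decisions to the observing physician when an event is found. The visible text gives no common question or interval for the two arms.

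Contact differs between arms. Section 2.7.2.1.2.3 gives the acupuncture arm a fixed course: "There will be 2 sessions per week for 12 weeks, giving 24 sessions in total". The rest is shared:

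- Section 2.7.1 applies the lifestyle programme to everyone ("Patients in both groups will receive basic health management and lifestyle modification over the course of the 12-week study period"), with "Prediabetes health education courses will be performed once a month".
- The same section adds remote contact of unstated frequency: "The researchers supervised the implementation of the prevention and treatment plan through telephone or Internet follow-up".
- Section 2.8 has a blinded evaluator collect data at baseline and weeks 4, 8, 12 and 24.

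Section 5 (Statistical analysis) describes the safety data first, and "then use tests to compare the incidence of adverse reactions between the 2 groups". It adds that the comparison should "consider the severity of adverse reactions and the degree of causation with the intervention". Section 4 states that patients and treating clinicians cannot be blinded. Table 1, the study timeline, is not shown.

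**The concern.** A between-arm test of incidence is interpretable only if an event of a given kind has the same chance of reaching the case report form in both arms. Here one arm meets a clinician every few days and the other about once a month, while recording depends on a reaction appearing or being found. A short-lived reaction noted at a needling session has no counterpart occasion in the control arm. The test could then partly measure how often patients were seen.

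A second problem lies in the mix of reactions. Several of those listed in section 3 (a bent needle, pain from needling, syncope during treatment) can arise only where needles are used. Their control-arm rate is zero by design, so a test of them answers no question. Pooling them with general reactions makes a single incidence comparison hard to read.

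At stake is the trial's statement on safety. Reactions missed during the trial cannot be recovered at analysis.

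**Working it through.** The plan gives no adverse-event rate and no safety figure to reproduce. The arm size used below follows from section 2.2: 25 per arm / (1 − 0.15) = 29.4, rounded up to 30, as stated.

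**Contact spacing (from the document).** 12 weeks = 84 days.
- Acupuncture: 84 / 24 sessions = 3.5 days between sessions.
- Shared contacts: visits at weeks 4, 8 and 12 are 84 / 3 = 28 days apart. Monthly courses are taken to fall at about the same times, giving 3 to 4 face-to-face contacts. This is an assumption. If courses and visits alternated, the spacing would be nearer 14 days.

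**Recording model (assumed).** Each patient has at most one transient reaction of a kind possible in either arm, with the same true rate in both arms. A contact captures it if it occurred within the last D days. Remote follow-up is set to zero. Then

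P(recorded) = min(1, D / contact interval).

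For D of 3.5 days or more, the acupuncture arm has P = 1. For controls P = D / 28:

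| Recall D (days) | Control coverage | Recorded rate ratio |
|---|---|---|
| 3.5 | 3.5/28 = 12.5% | 8 |
| 7 | 7/28 = 25% | 4 |
| 14 | 14/28 = 50% | 2 |
| 28 | 28/28 = 100% | 1 |

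**Effect on the test.** Recorded rate = true rate × coverage. The rejection probability is from exact enumeration of the two-sided Fisher test at 0.05 with 30 per arm and no true difference:

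| D (days) | True rate in both arms | Recorded, acupuncture vs control | P(Fisher p < 0.05) |
|---|---|---|---|
| 3.5 | 20% | 20% vs 2.5% | 0.37 |
| 3.5 | 40% | 40% vs 5% | 0.89 |
| 7 | 20% | 20% vs 5% | 0.24 |
| 7 | 40% | 40% vs 10% | 0.71 |
| 14 | 20% | 20% vs 10% | 0.10 |
| 14 | 40% | 40% vs 20% | 0.30 |
| 28 | 20% | 20% vs 20% | 0.022 |
| 28 | 40% | 40% vs 40% | 0.026 |

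The last two rows also show what equal enquiry with equal recall gives: false rejection of about 2.2% to 2.6%.

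**Sensitivity to the assumptions.**
- If remote follow-up were weekly and asked about reactions, control coverage at D = 7 would be 7/7 = 100% and the distortion would vanish. At D = 3.5 it would be 3.5/7 = 50%, a ratio of 2.
- With 14-day spacing and D = 7, coverage is 7/14 = 50%, again a ratio of 2.
- Lower true rates leave the ratio unchanged but make a significant result less likely, as the drop from 40% to 20% shows.
- The model covers only the 12 treatment weeks. From week 12 to week 24 no sessions are planned, so the later period dilutes any difference.

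**The case against.** The strongest case against has four parts.

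1. **Table 1 is not shown.** It may schedule adverse-event enquiry at the shared visits. Section 2.8 has data collected at weeks 4 and 8, where section 2.10 places no glucose, glycosylated haemoglobin or lipid measurement, so safety may be what is collected there. A reader might infer that the plan fails to tie safety to the common visits. That cannot be established without the table. What remains is that, even with such a schedule, section 3 as worded also admits reactions noted at the 24 sessions, and these enter one arm only.

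2. **Most listed reactions belong to needling.** For these, equal true rates do not apply, and a difference would be real. This stands and limits the point to reactions that either arm can have. It also supports separating the two kinds.

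3. **Section 5 weighs causation and severity.** This bears on misattribution, so one cannot say that events due to the lifestyle programme will be credited to acupuncture. But a causality judgement works only on recorded reactions and cannot restore control-arm reactions that nobody elicited.

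4. **The recall windows are assumptions.** Section 3 covers the whole test period and records onset date, frequency and duration, which permits retrospective capture. Remote follow-up applies to both arms. Both could remove the distortion. A reader might infer from the contact counts that equal true rates would be recorded as unequal; the document supports only that they could be.

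**Conclusion.** The point holds in limited form. Open recording, 24 additional contacts in one arm and a between-arm test of incidence are all stated, and together they leave the comparison exposed to unequal ascertainment for reactions possible in either arm. The size ranges from none to a recorded rate ratio of 8 with no true difference. At 30 per arm and 7-day recall, false rejection would be 0.24 at a true 20% and 0.71 at a true 40%, against 0.022 and 0.026 with 28-day recall.

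These figures rest on assumed recall windows, assumed true rates, 28-day spacing of control contacts and no remote enquiry. They illustrate a range and do not predict what this trial will record. For needle-only reactions the conclusion needs no assumption: controls cannot have them, so a between-arm test is uninformative.

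**What to change.** In section 3, ask both arms the same short adverse-event question, covering the whole interval since the last visit, at the existing visits at weeks 4, 8, 12 and 24. If Table 1 already schedules this, refer to it.

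Use a self-completed item on the case report form, or have existing staff other than the blinded evaluator ask the question. A reply that mentions needle pain or bleeding would reveal the allocation, so the evaluator should not hear the answers.

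In section 5, base the between-arm test only on reactions from that common enquiry that can occur in either arm. Report needling complications and other reactions noted at sessions descriptively, for the acupuncture arm alone and without a test.

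The cost is one form item at visits already planned and a sentence in each section. Sample size and visit schedule do not change. The small downside is reliance on 4-week and, at the last visit, 12-week recall, which will miss some minor transient reactions in both arms alike.

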## Blinding

4

Owing to the nature of this study, it is not possible to blind the patient or the clinician providing the intervention to the treatment received. The outcome assessor will be blinded to group allocation, unaffiliated with the treatment sites and not involved in providing the interventions.

## Statistical analysis

5

In this study, the conversion rate from IGT to normal blood glucose between baseline and follow-up period was the main outcome indicator. Statistical analysts will use a one-sided *t* test to compare between the 2 groups. The 2 groups will be compared using the 95% confidence interval method to determine the advantage. Data will be statistically analyzed using PASW Statistics 18.0 (IBM SPSS Inc., Armonk, NY) and SAS 9.2 software (SAS Institute Inc., Cary, NC). For secondary results, a 2-tailed *P* value *<* .5 will be considered statistically significant. For safety evaluation and analysis, first use descriptive analysis, and then use tests to compare the incidence of adverse reactions between the 2 groups. When comparing, consider the severity of adverse reactions and the degree of causation with the intervention. The categorical variables between the 2 groups were compared using Fisher exact test and chi-square test.

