### Sample size

2.2

The sample size calculation is based on the 2017 randomized controlled trial report of Ning et al^[8]^ who used acupoint catgut embedding to treat prediabetic patients. In this study, the reversal rate of impaired glucose regulation to Normal Glucose Tolerance is estimated as the outcome. We assume that after 3 months of treatment, the reversal rate of the treatment group is 57% and the reversal rate of the control group is 20%. The test levels (α = 0.05 and β = 0.2) are set. The PASS 2008 software (Beijing HuanZhongRuiChi Technology Co., Ltd.) calculates that the sample size of each group is 25, and 50 in the 2 groups. Assuming 15% drop out, a total of 60 participants will be needed to achieve statistical significance, so each group is required to have 30 participants.

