### Primary outcomes

2.9

The Primary outcomes is the conversion rate from prediabetes to normal blood glucose. Normal blood glucose means FBG and 2-hPG (OGTT) are in the normal range (FBG < 6.1 mmol/L, 2-hPG < 7.8 mmol/L).

Conversion rate = cases converted to normal blood glucose ÷ total cases of each group ×100%

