### Secondary outcomes

2.10

Secondary outcomes include the following: FPG, 2-hPG after a 75-g OGTT, glycosylated hemoglobin and blood lipid concentration.

FBG and 2h-hPG will be tested at visit 1 (3 days before study), visit 4 (week 12) and the end of follow-up period. Other secondary outcomes will be tested only at visit 1 and visit 4 (Table 1).

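### The primary time point is inconsistent: the sample size uses 3 months, the analysis section speaks of the follow-up period, and glucose is measured at both week 12 and week 24

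*Protocol article*

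**What the plan says.** Four parts of the protocol article bear on when the primary outcome is read.

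- Section 2.2 (Sample size): "We assume that after 3 months of treatment, the reversal rate of the treatment group is 57" per cent, and "the reversal rate of the control group is 20" per cent. Treatment lasts 12 weeks (sections 2.7 and 2.7.2), so this is the week-12 visit.
- Section 5 (Statistical analysis): "the conversion rate from IGT to normal blood glucose between baseline and follow-up period was the main outcome indicator".
- Section 2.8 (Outcome measures) lists data collection at baseline, "the intervention phase (4 weeks, 8 weeks, and 12 weeks) and at the end of follow-up (24 weeks". Section 2.10 (Secondary outcomes) makes the same separation: "FBG and 2h-hPG will be tested at visit 1 (3 days before study), visit 4 (week 12) and the end of follow-up period".
- Section 2.9 (Primary outcomes): "The Primary outcomes is the conversion rate from prediabetes to normal blood glucose". It then gives the glucose thresholds and the formula for the rate, but no visit.

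**The concern.** A binary primary outcome is not fully defined until its visit is fixed. Here the number that sized the trial belongs to the end of treatment. The sentence that introduces the main analysis uses a word that the article elsewhere reserves for a phase ending 12 weeks after treatment stops. Both glucose measurements that make up the outcome are scheduled at both visits, so either version can be computed from the data.

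Two things are at stake. If the choice stays open until the data are seen, whichever visit looks better can be reported as primary, and the nominal 5% level no longer holds. This matters more because section 4 says that patients and treating clinicians are not blinded. Second, if week 24 is what the authors mean, the trial is sized on rates for a different visit, and the article states none for week 24.

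**Working it through.** **Step 1: reproduce the plan's own figure.** Inputs from section 2.2: p1 = 0.57, p2 = 0.20, α = 0.05, β = 0.2, 15% dropout. The usual two-proportion formula with pooled variance under the null is

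n = [z(α)·√(2p̄(1−p̄)) + z(β)·√(p1(1−p1) + p2(1−p2))]² / (p1−p2)², with p̄ = 0.385.

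The two square roots are 0.688 and 0.637.

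- Two-sided: (1.960 × 0.688 + 0.842 × 0.637)² / 0.37² = 25.9, so 26 per group. The unpooled version gives 23.2, so 24.
- One-sided: 20.3, so 21 per group without continuity correction; 26 with it.

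The stated 25 lies between 24 and 26. Dropout: 25 / 0.85 = 29.4, so 30 per group and 60 in all, as stated. The sample size is therefore acceptable on its own inputs, and those inputs belong to 3 months only.

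**Step 2: set the time statements side by side.**

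| Section | Time stated for the outcome or its components |
|---|---|
| 2.2 | 3 months of treatment |
| 2.8 | weeks 4, 8 and 12 as the intervention phase; 24 weeks as the end of follow-up |
| 2.9 | none |
| 2.10 | fasting and 2-hour glucose at visit 1, week 12 and the end of follow-up |
| 5 | baseline to the follow-up period |

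In the terms of sections 2.8 and 2.10, section 5 points toward week 24, while section 2.2 is week 12. Nothing in the text shown says which governs.

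**Step 3: illustrate the error rate if either visit could count.** Section 5 states a one-sided test. With critical value 1.645 at each visit and correlation ρ between the two test statistics (assumed; the article gives none), the type I error is 1 − P(Z1 < 1.645, Z2 < 1.645).

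- ρ = 0: 1 − 0.95² = 9.75%
- ρ = 0.5: 8.8%
- ρ = 0.8: 7.5%
- ρ = 0.9: 6.8%

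**Step 4: illustrate power if week 24 is primary.** Take 25 evaluable per arm and control at 20%. Let a share of the 37-point difference persist (assumed; the article gives no 24-week rates). A share of 80% gives 0.20 + 0.8 × 0.37 = 0.496, and 70% gives 0.20 + 0.7 × 0.37 = 0.459. Power is Φ{[(p1−p2)·√25 − z(α)·√(2p̄(1−p̄))] / √(p1(1−p1)+p2(1−p2))}.

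| Treated rate at week 24 | One-sided 5% | Two-sided 5% |
|---|---|---|
| 0.57 (all persists) | (1.850 − 1.645 × 0.688)/0.637 = 1.13, power 87% | 78% |
| 0.496 (80%) | (1.480 − 1.645 × 0.674)/0.640 = 0.58, power 72% | 60% |
| 0.459 (70%) | (1.295 − 1.645 × 0.665)/0.639 = 0.32, power 62% | 50% |

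The one-sided column matches the test in section 5. The two-sided column is shown because section 2.2 does not state sidedness and its 25 per group lies close to the two-sided results.

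**The case against.** The best defence is that the conflict hangs on one loose phrase. Section 5 gives no week and does not say end of follow-up, which is the expression used for the 24-week visit in sections 2.8 and 2.10. Section 2.7.1 uses follow-up for telephone or internet contact in the lifestyle programme, which runs over the 12-week study period. On that reading the phrase means only a later assessment compared with baseline, and section 2.2 supplies the sole explicit time. The abstract also mentions the primary outcome shortly after the 3-month treatment course. This is also a condensed article: the silence of section 2.9 is no fault by itself, and Table 1 and Figure 1, which are not shown, may mark the intended visit.

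Part of this stands. A reader might infer that section 5 makes week 24 primary; it suggests that without stating it. The omission in section 2.9 should not be counted on its own. But the loose reading does not settle the matter, because a window running from baseline into follow-up contains both glucose visits. A visit schedule would not by itself say which visit is primary, nor would it remove the differing wording in sections 2.2 and 5.

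The numerical harm is also open to challenge. A reader might infer that the trial is underpowered or that its stated power fails. The document does not support that: it gives no 24-week rates and no sign that the effect fades, and section 1 describes a lasting effect for the related catgut-embedding therapy. Nor does anything say that the investigators will test both visits and report the better one.

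**Conclusion.** The point holds as an inconsistency in the primary time point. Section 2.2 places it at week 12, section 5 describes a span that in the article's own vocabulary reaches toward week 24, and section 2.9 does not decide between them. This is conflicting text within one document, not detail left to an analysis plan.

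The figures are illustrations only. The type I error of about 7.5% to 8.8% assumes correlations of 0.8 to 0.5 and that success at either visit would be claimed. The fall in one-sided power from about 87% to 72% or 62% (two-sided, 78% to 60% or 50%) assumes week 24 is primary, control stays at 20%, and 80% or 70% of the difference persists. With full persistence power does not change. The sample size itself reproduces to within one or two patients per group for 3 months and is not in question here.

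**What to change.** Name one primary time point, in the same words, in sections 2.9 and 5, and list conversion at the other visit as a secondary outcome. Week 12 (visit 4) is the natural choice because it is the only visit with stated planning rates, and section 2.2 then needs no change. A sentence such as this would do: the primary outcome is the proportion converted to normal blood glucose at week 12 (visit 4); conversion at week 24 is a secondary outcome describing durability.

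If the authors intend week 24, section 2.2 must state and justify the expected rates in both groups at week 24 and recalculate the sample size from them.

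With week 12 as primary, the cost is wording in two sections. Both visits and both glucose tests are already scheduled, so no patient, visit or test is added. With week 24, the cost also includes a new sample-size justification and possibly more patients. In either case the choice should be recorded before any outcome data are seen by group.

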**Methods and analysis::**

This study is a prospective randomized controlled trial in which 60 patients with prediabetes will be randomly allocated in a 1:1 ratio into either an acupuncture treatment group or a control group. Prediabetes patients in the control group will receive prediabetes health education for lifestyle interventions, whereas patients in the acupuncture group will receive lifestyle interventions plus Zuo Daliji and Yueku stitch treatment. Twenty-four treatment sessions will be performed over 3 months. The primary outcome is conversion rate from prediabetes to normal blood glucose. Secondary outcomes include fasting plasma glucose, 2-hour plasma glucose, glycosylated hemoglobin and blood lipid concentration.

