### Inclusion criteria

2.4

Participants meeting the following inclusion criteria will be included:

(1)Meet the diagnostic criteria of prediabetes:Participants meet one or both of the following criteria can be diagnosed. (According to the WHO criteria for a diagnosis of prediabetes in 1999^[13]^ which is cited by the Guidelines for the prevention and treatment of type 2 diabetes in China [2017 edition]^[10]^):**Impaired Fasting Glucose**: 6.1 mmol/L ≤ fasting plasma glucose (FPG) < 7.0 mmol/L, and 2-hour plasma glucose (2-hPG) after a 75 g oral glucose tolerance test (OGTT) <7.80mmol/L.**IGT**: FPG < 7.0 mmol/L, and 7.8 mmol/L ≤ 2-hPG (OGTT) < 11.1 mmol/L(2)Aged 18 to 65 years (either sex)(3)Voluntary participation and informed consent signed

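### The statistical analysis section names conversion from IGT as the main outcome, while the abstract, sample size, eligibility and outcome definition all cover prediabetes as a whole (IFG and/or IGT)

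*Protocol article*

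**What the plan says.** The article states the primary outcome, or the population it applies to, in five places.

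- **Abstract, Methods and analysis:** "The primary outcome is conversion rate from prediabetes to normal blood glucose".
- **Section 2.2, Sample size:** "the reversal rate of impaired glucose regulation to Normal Glucose Tolerance is estimated as the outcome". The Introduction uses impaired glucose regulation as another name for prediabetes, covering impaired fasting glucose, IGT, or both.
- **Section 2.4, Inclusion criteria:** "Participants meet one or both of the following criteria can be diagnosed". The two criteria are IFG (fasting glucose from 6.1 to below 7.0 mmol/L, 2-hour glucose below 7.80 mmol/L) and IGT (fasting glucose below 7.0 mmol/L, 2-hour glucose from 7.8 to below 11.1 mmol/L).
- **Section 2.9, Primary outcomes:** "The Primary outcomes is the conversion rate from prediabetes to normal blood glucose". Normal means both values in range ("FBG < 6.1 mmol/L, 2-hPG < 7.8 mmol/L"), and the formula is "Conversion rate = cases converted to normal blood glucose ÷ total cases of each group ×100"%.
- **Section 5, Statistical analysis:** the main outcome, taken from baseline to follow-up, is "the conversion rate from IGT to normal blood glucose".

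The first four agree on prediabetes as a whole. Section 5 alone names IGT.

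**The concern.** IGT is not a loose synonym for prediabetes in this article. The Introduction lists it as one of two prediabetic states, and section 2.4 gives it its own glucose criterion. Section 5 therefore names a narrower starting population than the one that is recruited, sized for and defined in section 2.9.

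The conflict sits in the section that an analyst would follow, and it concerns who contributes to the primary endpoint. Nothing in the article says which statement prevails. An analysis confined to IGT would use fewer participants than section 2.2 planned for. It would also answer a question about IGT, whereas the stated objective concerns prediabetes.

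This is not detail left to a fuller document. The article makes two statements of the primary outcome that cannot both be followed.

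**Working it through.** **Step 1: who is affected.** The IFG criterion requires a 2-hour value below 7.80 mmol/L and the IGT criterion requires at least 7.8 mmol/L. As written, they do not overlap. Everyone admitted under the IFG criterion has isolated IFG and does not have IGT. Participants with both values raised enter under the IGT criterion, which only asks for fasting glucose below 7.0 mmol/L.

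**Step 2: the two rules side by side.**

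| Participant at entry | Section 2.9 | Section 5, read literally |
|---|---|---|
| IGT, with or without raised fasting glucose | Converter if both values become normal | Same |
| Isolated IFG | Converter if fasting glucose falls below 6.1 mmol/L and the 2-hour value stays below 7.8 mmol/L | No IGT to convert from, so outside the endpoint |

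The rules differ only for isolated IFG. For those participants section 2.9 gives a workable answer and section 5 gives none.

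**Step 3: the plan's own figure.** Inputs from section 2.2: rates 0.57 and 0.20, α = 0.05, β = 0.2, 25 per group, 15% dropout. The section does not state sidedness.

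Pooled normal approximation, with mean rate (0.57 + 0.20)/2 = 0.385:

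- √(2 × 0.385 × 0.615) = 0.688
- √(0.57 × 0.43 + 0.20 × 0.80) = 0.636
- n = (z_α × 0.688 + 0.842 × 0.636)² / 0.37²

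Two-sided (z = 1.960) this gives 26 per group. The unpooled two-sided version gives 24, and the one-sided version with continuity correction gives 26. The stated 25 lies within this range. The uncorrected one-sided version (21) and the corrected two-sided version (32) do not reproduce it. For dropout, 25/0.85 = 29.4, hence 30 per group and 60 in total, as stated.

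**Step 4: illustration of an IGT-only analysis.** Two inputs are assumptions that the article does not supply:

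- an isolated-IFG share of 20% to 40%;
- 57% versus 20% holding unchanged within IGT.

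The evaluable number per group becomes 25 × 0.8 = 20 or 25 × 0.6 = 15. Power is Φ[(0.37 × √n − z_α × 0.688) / 0.636].

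| Analysed per group | One-sided 0.05 | Two-sided 0.05 |
|---|---|---|
| 25 (all prediabetes) | 87.0% | 78.5% |
| 20 (20% isolated IFG) | 79.4% | 68.5% |
| 15 (40% isolated IFG) | 68.2% | 55.3% |

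The one-sided column takes its sidedness from section 5, which specifies a one-sided primary test, and its level from section 2.2. The two-sided column is shown because the stated 25 also agrees with a two-sided calculation.

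**The case against.** The best reply is that this is one wrong abbreviation. Section 2.9 is the only place that defines the endpoint operationally, with thresholds, numerator and denominator. Section 5 sets up no IGT analysis set, excludes nobody by name and changes no formula. With four statements against one, a careful reader can recover the intended population. All of that stands, and it makes a drafting slip the likeliest explanation. It does not make section 5 correct: the sentence still names a different starting state for the main outcome.

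The reply also has force on size. The isolated-IFG share is not in the article, and the 57% and 20% rates are not given by subtype. On the one-sided test in section 5, a 20% share would leave power at 79.4%, close to the planned 80%. The power figures are therefore an illustration and carry no weight in establishing the contradiction.

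A reader might infer more: that isolated-IFG participants stay in the denominator and count automatically as failures. The article does not support this. The numerator in section 2.9 is conversion to normal glucose, and isolated-IFG participants can achieve it. Automatic failure appears only if the starting state in section 5 is combined with the denominator in section 2.9, and the article nowhere states that combination.

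**Conclusion.** The contradiction is real and stands on the text alone. Section 5 limits the main outcome to conversion from IGT; the abstract and sections 2.2, 2.4 and 2.9 do not. Taken literally, section 5 leaves every isolated-IFG participant out of the primary endpoint, although section 2.9 includes them and can count them as converters.

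The effect on the trial depends on whether the literal wording is followed and on a share that the article does not give. Under the two assumptions in the working, power would fall by about 8 to 19 percentage points one-sided (87.0 − 79.4 = 7.6; 87.0 − 68.2 = 18.8) or about 10 to 23 points two-sided (78.5 − 68.5 = 10.0; 78.5 − 55.3 = 23.2). If section 5 is brought into line with section 2.9, there is no loss from this source.

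It would go too far to conclude that the trial is planned as an IGT-only analysis or is underpowered for this reason. The rest of the article points to all prediabetes.

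**What to change.** In section 5, replace IGT with prediabetes (IFG and/or IGT) in the sentence naming the main outcome. Add a reference stating that conversion is defined as in section 2.9 (fasting glucose below 6.1 mmol/L and 2-hour glucose below 7.8 mmol/L), with the section 2.9 denominator, for all randomised participants.

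The cost is one changed term and one added sentence, to be made before the analysis. Eligibility, visits, the 25 evaluable per group and the 60 enrolled stay as they are.
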